### Sample size calculation and statistical considerations

Based on OS data reported by Kang et al. 2008 and by Sangro et al. 2010 [14, 37], in patients with locally advanced HCC median survival times of 9.35 months for Sorafenib-treated patients and 14 months for patients treated with Y-90 microspheres are assumed. This represents the minimum clinically meaningful difference to be detected.

Group-sequential methods are used to determine the sample size and study duration. Two interim analyses and a final analysis are planned to occur at equally spaced intervals after one-third, two-thirds and all of the planned number of deaths (events) have been reported. The planned sample size is determined assuming the use of a 2-sided log rank test with type I error of 0.05 and statistical power of 90 %. A dropout rate of up to 20 % is also factored into the computations. The anticipated study duration is 5 years; with 3 years of accrual and 2 years follow-up. This corresponds to an estimated hazard rate of 0.67 with an expected 266 deaths at the end of the study

The number of patients required for randomisation to detect a clinically relevant difference in OS time with SIRT versus Sorafenib was determined to be 360 patients (180 patients in each treatment arm).

### Interim analyses

Interim analyses for efficacy are planned after 33 and 65 % of the information (corresponding to 87/266 and 174/266 deaths) have been observed and using a critical *p*-value of *p* ≤ 0.0001 for the first analysis and *p* ≤ 0.015 for the second analysis These boundaries are obtained using the method of Lan and DeMets [38] and based on an overall significance level of 5 %. The final analysis will be performed after 266 reported deaths.

An independent Data Monitoring Committee will review the safety of the study and the results of the interim analyses and make appropriate recommendations to the trial steering committee. .

### Statistical analyses

All analyses will be performed using the intention-to-treat (ITT) principle where patients will be analysed according to their randomised group. The analysis of the primary outcome (OS) will be an unadjusted log rank test used to test and a proportional hazards model will be use to estimate the hazard ratio together with the corresponding 95 % confidence intervals (CI). Time to event curves (for OS and PFS) will be displayed using the method of Kaplan-Meier.

The tumour response rate, disease control rate and the rate of down-staging to surgical resection, radiofrequency ablation or liver transplantation compared between treatments using appropriate tests for proportions

HRQoL will be analysed using generalised estimating equations assuming a common (exchangeable/compound symmetric) correlation structure, following the guidelines of the EQ-5D questionnaire.

A Landmark analysis will be performed at 2-months post-randomization comparing patients classified into four groups: Those randomised to Sorafenib and (i) but did not receive 80 % of scheduled dose since randomization; (ii) those receiving at least 80 % of the scheduled dose; and, those randomized to SIRT therapy and (iii) did not receive the therapy; (iv) those who receiving the SIRT therapy within the first two months of randomization [39]. This analysis will be repeated using 40 and 60 % scheduled doses since randomization for defining groups (i) and (ii). These comparisons will be performed for the primary and secondary outcomes. Patients who died or discontinued the study before 2-months of randomization will not be included from the analysis. Additional sub-group analyses will be performed based on patients’ baseline characteristics such as presence or absence of portal vein thrombosis, BCLC stage, prior HCC treatment, hepatitis status, ECOG performance status, tumour size (≤50 % of liver, > 50 % of liver), age (<65 years, ≥65 year), and gender.

As the SIRT therapy is a local treatment, treatment effect of progression in the liver as the first event will be investigated using a competing risk analysis. In this analysis death or progression outside the liver as the first event will be considered as a competing risk for liver progression. The method of Gray [40] will be used to compare groups with hazard ratios and 95 % CI estimated from the proportional hazards approach detailed by Fine and Gray [41]. Time to liver progression in the two groups will be displayed using cumulative incidence curves.

Toxicity will be reported according to NCI CTCAE Version 4.02 criteria.

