### Treatment

Treatment in the Sorafenib arm will commence within 1 week after randomisation. Patients will receive oral Sorafenib, 400 mg twice daily. Sorafenib treatment will be continued until there is evidence of treatment failure (lack of efficacy resulting in tumour progression at any site determined by CT or MRI scan); there is a cure or complete response and/or the patient undergoes surgical resection, liver transplantation or ablative therapy; unacceptable toxicity occurs; or the patient requests an end to treatment. As published previously, doses may be delayed and/or reduced for clinically significant haematological toxicities and other toxicities or adverse events (AEs) related to study therapy. Dose reductions first to 400 mg/day and then to 400 mg every second day will be allowed, and if further dose reductions are required the patient should be discontinued. For non-haematological AEs other than skin toxicity, treatment will be interrupted for any grade 3 AE, and the dose subsequently reduced by one level. For skin toxicity, treatment will be interrupted for any grade 2 or grade 3 AE and a decreased dose frequency or level will be subsequently considered. The dose may be re-escalated once the toxicities or AEs have resolved [31].

Patients randomised to SIRT will receive SIR-Spheres at the patient-specific prescribed activity within 35 days after signing of informed consent form, and after the baseline assessment of their suitability for the procedure. The assessment comprises a hepatic angiogram, and a liver-to-lung shunt pre-assessment with Technetium-99 m (^99m^Tc)-labelled human serum albumin. The hepatic angiogram will determine the vascular anatomy of the liver in order to plan the optimal delivery of the SIR-Spheres. The ^99m^Tc lung-shunt study will assess the presence and degree of lung shunting from the liver. Patients randomised to SIRT, but who are found to be unsuitable for treatment will be included in the SIRT intention to treat analysis. The prescribed activity of SIR-Spheres® will be calculated based on the patient’s body surface area (BSA) model [32], or the partition model [33]. If the BSA method is used for dose calculation and the percentage lung shunting exceeds 20 % of the hepatic artery blood flow, as determined by ^99m^ Tc-scan, the partition model may be used to adjust the prescribed activity so that the radiation absorbed dose to the lungs does not exceed 20 Gy.

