AE/SAE	AE/SAE for the Sorafenib arm will be recorded from the time of signing the ICF until 30 days after the final dose of Sorafenib, or until commencement of the next alternative therapy, whichever is earlier. AE/SAE for the SIRT arm will be recorded from the time of signing the ICF until 30 days post-SIRT regardless of causality and for a further 5 months thereafter if judged by the investigator to be causally related to SIRT or Sir-Spheres, or until commencement of the next alternative therapy, whichever is earlier. If the AE/SAE is a Sorafenib or SIRT related toxicity follow-up will continue until resolution.							
Survival								X

^a^Screening assessments performed within 28 days before signing of informed consent can be used to confirm eligibility

^b^Sorafenib arm only. Sorafenib patients contacted at Week 2 to assess treatment related toxicity and interrupt/modify the dose as necessary

^c^Disease progression, death, complete regression, unacceptable toxicity, patient responds to treatment and becomes eligible for surgical resection, liver transplantation or ablative therapy, lost to follow-up, patient’s request for withdrawal

^d^Concomitant medication to be recorded from screening up to 30 days post-study conclusion, or until commencement of the next alternative therapy, whichever is earlier

^e^If either the Hepatitis B Surface Antigen (Hep Bsag) test or anti-HCV IgG test is positive, the other test will be optional. Hepatitis B Core Antibody IgG test is optional

^f^Women of reproductive potential must have a negative pregnancy test before commencing treatment. Test to be repeated if pregnancy is suspected during the study

^g^Hepatic angiogram and ^99m^Tc-MAA lung shunt study to be performed after randomisation and prior to treatment commencement only for SIRT arm group

^h^The same radiological assessment method must be used throughout the study

^i^ Assessment for tumour response rate to be done every 12 weeks from date of randomisation until first evidence of disease progression

Study conclusion is defined as disease progression, death, complete regression, unacceptable toxicity, patient-undergoing surgical resection, liver transplantation or ablative therapy due to a sufficient response with therapy, loss to follow-up, or patient’s request for withdrawal.

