### Outcome measures

The primary endpoint of the SIR*ve*NIB trial is overall survival (OS). Secondary endpoints include: time to progression (TTP), progression-free survival (PFS), overall and in the liver; tumour response rate (assessed by Response Evaluation Criteria in Solid Tumours [RECIST] version 1.1) [35]; disease control rate; health-related quality of life (HRQoL); safety and toxicity; and liver resection rate and liver transplantation rate.

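### The intention-to-treat rule is stated for every analysis with no exception for toxicity, so patients never given SIR-Spheres will lower the apparent SIRT toxicity rate

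*Protocol article*

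**What the plan says.** All points are from the protocol article.

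- **Analysis set.** Statistical analyses opens with a rule that has no exception: "All analyses will be performed using the intention-to-treat (ITT) principle where patients will be analysed according to their randomised group".
- **Toxicity as an endpoint.** Outcome measures includes "safety and toxicity" among the secondary endpoints.
- **Toxicity analysis.** The only further statement is on grading: "Toxicity will be reported according to NCI CTCAE Version 4.02 criteria". No other population is named for it.
- **When suitability for SIRT is found out.** A footnote to the schedule table under Assessments reads: "Hepatic angiogram and ^99m^Tc-MAA lung shunt study to be performed after randomisation and prior to treatment commencement only for SIRT arm group".
- **What happens to unsuitable patients.** Treatment says: "Patients randomised to SIRT, but who are found to be unsuitable for treatment will be included in the SIRT intention to treat analysis".
- **Untreated patients are expected.** One landmark group under Statistical analyses is "those randomized to SIRT therapy and (iii) did not receive the therapy".
- **Adverse event window.** The schedule table says: "AE/SAE for the SIRT arm will be recorded from the time of signing the ICF until 30 days post-SIRT regardless of causality". It then allows a further 5 months for events judged related to SIRT. In both arms, recording ends when the next alternative therapy begins, if that comes first.
- **Purpose.** The Discussion says that the trial allows a comparison of the toxicity caused by the two treatments.

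**The concern.** Intention to treat is the right basis for overall survival: it protects the randomised comparison and usually works against a false claim of superiority. For harms it tends to work the other way. A patient who never received SIR-Spheres cannot have toxicity caused by them, yet counts in the denominator and makes the treatment look safer.

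Here non-treatment in the SIRT arm is built into the design, because the work-up that decides suitability follows randomisation and is done in that arm only. Sorafenib is to start within 1 week of randomisation with no comparable gate. The dilution will therefore fall mainly on the experimental arm, in its favour, in a comparison that the article presents as one of the trial's purposes.

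This is not a complaint that a safety population is undefined, which an article may leave to the full protocol or analysis plan. The article makes a positive statement that, read plainly, covers toxicity. An analysis plan with an as-treated safety set would contradict it.

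**Working it through.** **Does the rule reach toxicity?** Toxicity is a listed endpoint, the rule covers every analysis, and the toxicity sentence gives grading criteria only. On a plain reading, yes.

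**Inputs**
- Patients randomised to SIRT: 180 (Sample size calculation and statistical considerations).
- u, the share of the SIRT arm never treated: not given; assumed 5, 10, 20 and 30%.
- p_T, the rate of a given toxicity among treated patients: not given; assumed 30%.
- p_U, the rate among untreated patients: not given; assumed 0% or 10%. Zero fits toxicity caused by SIR-Spheres. A value above zero fits events of any cause, since recording starts at consent and so takes in work-up and disease events.

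The article gives no toxicity rate or untreated share, so there is no planned figure to reproduce first. The planned 266 deaths do not enter this calculation.

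**Formula**

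Rate shown by randomised group = (1 − u) × p_T + u × p_U

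**Results with p_T = 30%**

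| u | Treated, of 180 | Untreated | Shown if p_U = 0% | Shown if p_U = 10% |
|---|---|---|---|---|
| 5% | 171 | 9 | 0.95 × 30 = 28.5% | 28.5 + 0.5 = 29% |
| 10% | 162 | 18 | 0.90 × 30 = 27% | 27 + 1 = 28% |
| 20% | 144 | 36 | 0.80 × 30 = 24% | 24 + 2 = 26% |
| 30% | 126 | 54 | 0.70 × 30 = 21% | 21 + 3 = 24% |

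With p_U = 0, the rate shown is the treated-patient rate times (1 − u), whatever that rate is. An assumed 20% rate, for example, shows as 18, 16 or 14% at u = 10, 20 or 30%.

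**Direction.** The rate falls whenever p_U is below p_T. For toxicity caused by SIR-Spheres this always holds, because p_U is zero. For events of any cause it depends on work-up and disease events in untreated patients, and the loss is smaller.

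**Does the landmark analysis supply an undiluted comparison?** It separates SIRT-randomised patients by whether they received SIRT in the first two months, and it applies to secondary outcomes. But it leaves out patients who died or discontinued before 2 months. Unacceptable toxicity is one of the article's study-conclusion events, so the exclusion can remove patients with the worst early toxicity.

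**The case against.** **The article is condensed, and its word all may not be meant strictly.** Toxicity gets one descriptive line with no test or denominator, and the landmark analysis in the same section itself groups patients by treatment received. This stands in part: the sponsor may intend a treated-patient safety set. But the sentence as published says otherwise and needs correcting in either case.

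**The landmark analysis already shows treated and untreated patients apart.** True, so a diluted table is not the only view planned. It does not replace a safety set, because it drops early deaths and discontinuations.

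**Non-treatment can also occur on sorafenib.** Correct. Patients may never start or may ask to stop, and the article gives no rate for either arm. The supportable statement is that the dilution falls mainly in the SIRT arm, not only there.

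**The size is assumed.** Correct. The direction follows from the design; the figures illustrate it.

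Two stronger readings are tempting, and the article does not support them:
- A reader might infer that toxicity from substitute sorafenib would be counted as SIRT experience. Recording stops in both arms when the next alternative therapy starts, so new events on that therapy are not brought in.
- A reader might infer that the adverse event window has no end for every untreated SIRT-arm patient. It closes for those who move to another therapy. Within that arm, only patients who receive neither SIRT nor another therapy have no end date.

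**Conclusion.** The point holds as a fault in a stated rule. Applied as written, the analysis by randomised group puts patients never given SIR-Spheres into the SIRT toxicity denominator, lowers the apparent SIRT rate, and works against the stated aim of comparing the toxicity each treatment causes.

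With 5 to 30% untreated and a 30% rate among treated patients, the understatement is 1.5 to 9 percentage points if untreated patients have no events, and 1 to 6 points if 10% of them do. All three rates are assumptions.

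The survival analysis, the sample size and the 266 planned deaths are untouched. This should be corrected, but it does not threaten the primary result.

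**What to change.** 1. Limit the intention-to-treat sentence under Statistical analyses to efficacy and health-related quality of life.
2. State that toxicity is analysed in patients who received at least one dose of sorafenib or any SIR-Spheres, grouped by the treatment received.
3. Report separately the events of the SIRT work-up and the adverse events of SIRT-randomised patients who were never treated, so that harms of the whole SIRT strategy stay visible.

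A changed analysis set does not close the narrow gap in the recording window. The documents should also say when adverse event recording ends for a SIRT-arm patient who receives neither SIRT nor another therapy.

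The analysis change takes a few lines of text and no new data. Trial status says that recruitment has closed and the final analysis awaits 266 deaths, so the rule can still be settled before that analysis. The downside is that the safety groups are no longer exactly the randomised groups, so the toxicity comparison loses some of the protection of randomisation. The separate reporting in step 3 lets readers see who was left out.

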### Overview of trial design

SIR*ve*NIB is a prospective, randomized open-label, multicentre trial comparing SIRT and Sorafenib in patients with locally advanced HCC. In SIR*ve*NIB, the aim will be to recruit a minimum of 360 patients from a minimum of 15 sites across the Asia-Pacific region.

Eligible patients will be randomized 1:1 to receive either systemic therapy with oral Sorafenib or a session of SIRT with SIR-Spheres® (Fig. 1). Randomisation will be stratified by centre and the absence or presence of PVT.

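### The primary log-rank test ignores portal vein thrombosis although randomisation is stratified by it; the test is valid, but mildly conservative and less efficient if PVT is prognostic

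*Protocol article*

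**What the plan says.** Under Overview of trial design: "Randomisation will be stratified by centre and the absence or presence of PVT". The abstract gives the same two factors. Under Statistical analyses, the primary test is fixed: "The analysis of the primary outcome (OS) will be an unadjusted log rank test". The effect estimate follows in the same sentence: "a proportional hazards model will be use to estimate the hazard ratio", with a 95% confidence interval. No covariates or strata are named for that model, and none are ruled out. In the analysis, PVT appears only as one of several baseline subgroup factors.

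The sample size section uses the same kind of test, "assuming the use of a 2-sided log rank test with type I error of 0.05", and mentions no stratification. Its inputs are overall medians: "median survival times of 9.35 months for Sorafenib-treated patients and 14 months for patients treated with Y-90 microspheres are assumed". The result is "an estimated hazard rate of 0.67 with an expected 266 deaths at the end of the study".

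**The concern.** Balancing the arms on a prognostic factor removes the chance imbalance in that factor from the treatment comparison. An unstratified log-rank test does not know this, and its variance still allows for such imbalance. If PVT predicts death, the standard error is therefore somewhat too large, and the test rejects less often than 5% under the null. Under the alternative, leaving out a prognostic factor also brings the marginal hazard ratio nearer to 1 than the within-stratum hazard ratio, which lowers power at a fixed number of deaths.

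What is at stake is efficiency in the test of the primary endpoint. The number of deaths is fixed at 266 and PVT status is already recorded for randomisation, so any lost power could be recovered without more patients or more follow-up. The article states the unadjusted test outright, so this is a choice made in the document and not a detail left to an analysis plan.

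**Working it through.** **Inputs from the article.** Medians 9.35 and 14 months; 360 patients, 1:1; 266 deaths; two-sided alpha 0.05; power 90%; accrual 36 months; at least 15 sites ("from a minimum of 15 sites across the Asia-Pacific region"). **Assumed, because the article does not give them:** PVT prevalence 30–40%; hazard ratio of PVT for death 1.0, 1.5, 2.0 or 2.5.

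**1. The plan's own figure.** HR = 9.35/14 = 0.668. With (1.960 + 1.282)² = 10.507:
- Freedman: 10.507 × [(1 + 0.668)/(1 − 0.668)]² = 10.507 × 5.0215² = 265 deaths.
- Schoenfeld: 4 × 10.507/(ln 0.668)² = 258 deaths.
- With Lan–DeMets O'Brien–Fleming looks at 87, 174 and 266 deaths, about 263 deaths are needed, and power at 266 is 90.3%.

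So 266 deaths and 90% power reproduce, and they refer to the unstratified test.

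**2. Simulation of the alternatives.** 360 patients, permuted blocks of 4 within 15 centres × PVT, data cut at the 266th death, one final look at |Z| > 1.96, within-stratum treatment HR 0.668. The stratified statistic is Z = Σ(O − E)/√ΣV, summed over strata. Results at 30% prevalence:

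| PVT HR | Power, unadjusted | Power, PVT-stratified | Gain (points) | Power, PVT × centre | Alpha, unadjusted | Alpha, PVT-stratified |
|---|---|---|---|---|---|---|
| 1.0 | 90.5% | 90.2% | about 0 | 86.5% | 4.9% | 5.0% |
| 1.5 | 89.4% | 90.3% | about 1 | 85.5% | 4.6% | 4.8% |
| 2.0 | 87.4% | 90.0% | about 3 | 85.8% | 4.5% | 5.0% |
| 2.5 | 85.5% | 90.6% | about 5 | 85.2% | 3.9% | 4.4% |

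Power comes from 4,000 replicates (Monte Carlo standard error about 0.5 points). Alpha comes from 12,000 replicates at 1.5 and 2.0 (about 0.2 points) and 4,000 at 1.0 and 2.5 (about 0.3 points).

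Over prevalences of 30–40%, power (unadjusted against PVT-stratified) is about 91 v 91%, 90 v 91%, 87–88 v 89–90% and 84–86 v 89–90%. Alpha of the unadjusted test is about 4.4–4.5% at a PVT hazard ratio of 2.0 and 3.7–4.1% at 2.5.

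**3. Hand check of the gain.** The mean estimated treatment HR (unadjusted against PVT-stratified, 30% prevalence) was 0.671 v 0.666, 0.680 v 0.665 and 0.691 v 0.666 for PVT hazard ratios of 1.5, 2.0 and 2.5. Put these into power = Φ(√(266/4) × |ln HR| − 1.96), with √66.5 = 8.155:
- 1.5: 90.2% v 91.2%, difference 1.0.
- 2.0: 88.1% v 91.3%, difference 3.3.
- 2.5: 85.3% v 91.2%, difference 5.9.

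The differences agree with the simulation to within a point.

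**4. If the marginal HR, and not the within-stratum HR, is near the planned value** (about 0.66 in these runs), the unadjusted test keeps about 91–92% power. The PVT-stratified test has about 92%, 93% and 95% for PVT hazard ratios of 1.5, 2.0 and 2.5. There is then no shortfall against the plan, but the stratified test is still the stronger one.

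**5. Centre.** 15 centres × 2 PVT levels = 30 cells, so 360/30 = 12 patients and 266/30 ≈ 9 deaths per cell on average. At 30% prevalence a PVT-positive cell averages 108/15 = 7 patients. Deaths in cells with only one arm left at risk carry no information. Hence the 85–86% power in the PVT × centre column, which is below the PVT-stratified test throughout and never above the unadjusted test.

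**The case against.** The strongest reply is that nothing is broken. An unadjusted log-rank test is valid, its type I error is not inflated, the trial was sized for that same test, and its 90% power reproduces. On this view the choice between two valid tests is a preference. All of this stands except the last step. When a factor is already used at randomisation, analysing by it costs practically nothing if it is not prognostic (90.2% against 90.5%, within simulation error) and gains power if it is.

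Second, the size depends on two figures that the article does not contain. This also stands, and it is why a range is given. At a moderate PVT hazard ratio of 1.5 the gain is only about 1 point.

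Third, consistency might seem to require stratifying on both randomisation factors, and that would cost power. This limits the recommendation to PVT alone.

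A reader might infer more than the article supports:
- *That the Cox model is unadjusted.* The word is attached only to the log-rank test. The form of the model is not stated.
- *That the reported hazard ratio would be biased.* The marginal and PVT-conditional hazard ratios are different estimands, and reporting the marginal one is legitimate.
- *That the Background shows PVT to be prognostic.* It suggests that SIRT may help more when PVT is present. That is effect modification, which the planned subgroup analysis addresses, and not evidence that PVT predicts death.
- *That 266 deaths or 360 patients are too few.* The recalculation does not show this.

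**Conclusion.** The mismatch is real and stated in the document: PVT is a stratification factor at randomisation and is absent from the primary test. It is a modest efficiency point, not a fault of validity or of sample size. Any loss is conditional on PVT being prognostic for death: none at a PVT hazard ratio of 1.0, about 1 power point at 1.5, about 3 at 2.0 and 4–6 at 2.5, with the actual alpha falling to about 4.4–4.5% at 2.0 and 3.7–4.1% at 2.5.

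These figures assume 30–40% prevalence, proportional hazards, a within-stratum treatment HR of 0.668 and a single final look at 0.05; the two interim looks are not simulated. The direction is secure if PVT is prognostic. The exact size is not, because the article gives neither the prevalence nor the effect of PVT.

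**What to change.** Before the final analysis, and blind to outcome by arm, amend Statistical analyses so that:
- the primary test of overall survival is a log-rank test stratified by PVT as recorded at randomisation;
- the hazard ratio and its confidence interval come from a Cox model stratified by PVT, so that test and estimate match;
- the unadjusted log-rank test is kept as a sensitivity analysis;
- the text says how centre is handled, and does not stratify the test by individual centre.

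The article does not say whether the interim efficacy looks at 87 and 174 deaths have taken place. If either has already used the unadjusted test, keep that test as primary, so that the test does not change partway through the sequence, and prespecify the PVT-stratified log-rank test and Cox model as the key sensitivity analysis.

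The cost is a short amendment. PVT status is already collected, and neither the 360 patients nor the 266 deaths change. Trial status reports recruitment closed and the final analysis still waiting for its deaths, so as of the article the change could still be made.

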### Outcome definitions

OS – the time from the date of randomisation to death from any cause.TTP – the time from the date of randomisation to tumour progression at any site in the body.PFS at any site – time from the date of randomisation to tumour progression at any site in the body or death, whichever is earlier.PFS in the liver –time from the date of randomisation to tumour progression in the liver or death whichever is earlier.Tumour response rate is the number of patients whose best overall response rate (best tumour response over the whole study between randomisation and the last tumour assessment) is partial response (PR) or complete response (CR), divided by the total number of patients in the analysis population.Disease control rate – the number of patients whose best overall response is PR, CR or stable disease (SD), divided by the total number of patients in the analysis population.HRQoL assessed using the EQ-5D questionnaire.Adverse events will be reported according to National Cancer Institute criteria (National Cancer Institute Common Terminology criteria for Adverse Events [NCI CTCAE] Version 4.02) [36].

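### The liver-progression analysis names only Gray's test, a Fine-Gray hazard ratio and liver incidence curves, which on their own cannot show whether SIRT slows progression in the liver

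*Protocol article*

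**What the plan says.** The last part of the Statistical analyses section of the protocol article gives the local action of SIRT as the reason for a further analysis: "treatment effect of progression in the liver as the first event will be investigated using a competing risk analysis". It defines the competing events: "death or progression outside the liver as the first event will be considered as a competing risk for liver progression". Three tools follow:

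- the test: "The method of Gray [40] will be used to compare groups";
- the effect measure: hazard ratios with 95% confidence intervals, "estimated from the proportional hazards approach detailed by Fine and Gray";
- the display: "Time to liver progression in the two groups will be displayed using cumulative incidence curves".

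The section names no cause-specific hazard ratio for liver progression, and no estimate or curve for the competing events.

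A related endpoint stands elsewhere. Outcome measures lists "progression-free survival (PFS), overall and in the liver", and Outcome definitions gives PFS in the liver as "time from the date of randomisation to tumour progression in the liver or death whichever is earlier". A footnote to Table 2 in Assessments limits the imaging: "Assessment for tumour response rate to be done every 12 weeks from date of randomisation until first evidence of disease progression".

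**The concern.** A Fine-Gray model works on the subdistribution hazard. Patients who have died or progressed outside the liver stay in the risk set for liver progression, although they can no longer have it as a first event. The hazard ratio, Gray's test and the cumulative incidence curve therefore all answer one question: what proportion of each arm has liver progression first? The reason given for the analysis, that SIRT acts locally, points to another: does SIRT change the rate of liver progression among patients still free of any event?

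The two answers agree when the competing events are equally frequent in both arms. That cannot be taken for granted here. One treatment is local and the other systemic, so first progression outside the liver may differ, and the sample size section itself assumes that survival differs. A conclusion about local control drawn from these three tools alone could then reflect deaths or extrahepatic progression instead.

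**Working it through.** **What the plan supplies.** The article gives no figure for the liver analysis, so there is none to reproduce. The one relevant input is the survival assumption in the sample size section: medians of 9.35 months (Sorafenib) and 14 months (SIRT). Under exponential survival the hazard ratio is 9.35/14 = 0.668, which matches the stated 0.67.

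**Assumed inputs.** Constant hazards per month: liver λL = 0.06, 0.10 or 0.15, identical in both arms, so that the true cause-specific hazard ratio is 1.00; competing hazard on Sorafenib λC = 0.04 or 0.08; competing hazard on SIRT = k × λC; follow-up of 24 months.

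**Formulas.** The cumulative incidence of liver progression is

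F(t) = λL/(λL + λC) × [1 − exp(−(λL + λC)t)].

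The subdistribution hazard is f(t)/[1 − F(t)], with f(t) = λL exp(−(λL + λC)t). The competing hazard enters both parts. The Fine-Gray ratio was obtained by solving the population score equation over 24 months.

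**One case in full.** λL = 0.10 in both arms, λC = 0.08 on Sorafenib and 0.12 on SIRT (k = 1.5).

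- Sorafenib: F(24) = 0.10/0.18 × (1 − exp(−4.32)) = 0.548.
- SIRT: F(24) = 0.10/0.22 × (1 − exp(−5.28)) = 0.452.
- The Fine-Gray ratio is 0.79. As a hand check, the ratio of ln(1 − F) is ln(0.548)/ln(0.452) = 0.76 at 24 months. At 12 months, where F is 0.422 and 0.491, it is ln(0.578)/ln(0.509) = 0.81. The value 0.79 lies between them.

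**All six combinations of λL and λC, no true liver effect.**

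| k (SIRT/Sorafenib competing hazard) | Cause-specific HR | Fine-Gray HR |
|---|---|---|
| 0.67 | 1.00 | 1.12 to 1.23 |
| 1 | 1.00 | 1.00 |
| 1.25 | 1.00 | 0.87 to 0.93 |
| 1.5 | 1.00 | 0.77 to 0.87 |
| 2 | 1.00 | 0.62 to 0.77 |

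With λL = 0.10 on Sorafenib and a liver rate 10% worse on SIRT (cause-specific HR 1.10), the Fine-Gray HR is still 0.86 to 0.92 at k = 1.5.

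**Effect on the test.** Each setting used 4,000 simulated trials of 180 per arm, all followed to 24 months, with no true liver effect. The table gives how often a two-sided 5% test favours SIRT (nominal 2.5%).

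| k | Settings | Gray's test | Cause-specific log rank |
|---|---|---|---|
| 1 | 1 | 2.9% | 2.6% |
| 1.5 | 4 | 23% to 35% | 2.1% to 2.8% |
| 2 | 2 | 59% to 62% | 2.6% to 2.7% |

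**Which direction is plausible.** Suppose the death hazard before progression follows the planned ratio of 0.67. If extrahepatic progression makes up half of the competing events on Sorafenib, its SIRT/Sorafenib ratio x must satisfy 0.5 × 0.67 + 0.5x = k. That gives x = 1.33 for k = 1 and x = 2.33 for k = 1.5. If it makes up one third, 0.67 × 2/3 + x/3 = k gives x = 1.66 and 3.16. Below the first value in each pair the distortion runs against SIRT; above it, in favour of SIRT. The article offers no data to choose between them.

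**The case against.** The plan is coherent as far as it goes. Gray's test, the Fine-Gray model and cumulative incidence curves all target the same quantity, and the choice between subdistribution and cause-specific hazards is a choice of estimand. A lower cumulative incidence on SIRT would be real; the error would lie in reading it as slower liver progression. The cause-specific ratio is no perfect measure of local control either, since it compares patients still event-free, whose mix may come to differ by arm. All of this stands, and it is why Fine-Gray should be supplemented and not displaced.

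Other endpoints would also reveal part of any harm elsewhere. Excess deaths on SIRT would count against it in overall survival and in both PFS endpoints; excess extrahepatic progression would count in TTP and any-site PFS. This stands in part. TTP and any-site PFS pool liver and extrahepatic progression, so they cannot separate them. PFS in the liver does not count extrahepatic progression, and because scheduled response assessment ends at first progression, later liver progression may go unseen. No listed endpoint gives the liver rate by itself.

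A reader might infer that the plan is set to produce a false liver benefit for SIRT. The documents do not support that. They give no liver, extrahepatic or competing-event rates; the survival assumption points the other way for deaths; and the Background says that patients often die before extrahepatic spread appears.

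Finally, a full protocol or analysis plan, not shown, may add the missing estimates. The point here is limited to the measures that the article does select and the purpose that it gives for them.

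**Conclusion.** The point holds as a limit on interpretation, with no fixed direction. The named tools mix the liver rate with the arms' rates of death and extrahepatic first progression, so taken alone they do not support a statement that SIRT does or does not slow liver progression. Under the assumed rates, a competing hazard differing by a factor of 1.5 moves a null liver effect to a Fine-Gray ratio of roughly 0.8 or 1.2, depending on which arm has the excess. These sizes rest on constant hazards, 24 months of follow-up and rates that the article does not supply; the mechanism does not depend on them. The analysis is supportive. The overall survival test, the 266 deaths, the interim boundaries and the sample size are unaffected.

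**What to change.** Before the final analysis, which the article says still awaits 266 deaths:

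1. Keep Gray's test, the Fine-Gray hazard ratio and the cumulative incidence curves, and label them as describing the absolute risk of liver progression as first event.
2. Add the cause-specific hazard ratio for liver progression, with its 95% confidence interval, from a Cox model that censors the competing events. Base any statement about the rate of liver progression on it.
3. Report cause-specific hazard ratios and cumulative incidence curves by arm for extrahepatic first progression and, separately, for death, so that a reader can see what drives any difference in the liver curves.

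The cost is a few more models on data already being collected, and one more table to explain for a supportive analysis.
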